## Abstract

**Background:**

Surgical site infections (SSIs) are the most common nosocomial infection and occur in 16.3% of patients undergoing colorectal surgery at our institution (The Ottawa Hospital), the majority of which are identified after discharge from hospital. Patients who suspect having an SSI generally present to the emergency department or surgery clinic. Both options for in-person interaction are costly to the health care system and patients. A mobile app, how2trak, has proven to be beneficial for patients with complex wounds at our institution by facilitating at-home monitoring and virtual consultations.

**Objective:**

This study aims to assess the feasibility of a randomized controlled trial to assess if how2trak can improve patients’ experience and increase detection of SSIs after colorectal surgery while reducing patients’ risk of COVID-19 exposure.

**Methods:**

In this single-center prospective feasibility trial, eligible patients undergoing colorectal surgery will be randomized to either standard care or how2trak postoperative monitoring of their incision, symptoms, and ostomy function. Patient self-assessments will be monitored by a nurse specialized in wound and ostomy care who will follow-up with patients with a suspected SSI. The primary outcome is feasibility as measured by enrollment, randomization, app usability, data extraction, and resource capacity.

**Results:**

This study was approved by our institution’s ethics board on February 26, 2021, and received support from The Ottawa Hospital Innovation and Care Funding on November 12, 2021. Recruitment started June 3, 2021, and 29 were patients enrolled as of September 2021. We expect to publish results in spring 2022.

**Conclusions:**

This study will determine the feasibility of using a mobile app to monitor patients’ wounds and detect SSIs after colorectal surgery. If feasible, we plan to assess if this mobile app facilitates SSI detection, enhances patient experience, and optimizes their care.

**Trial Registration:**

ClinicalTrials.gov NCT04869774; https://clinicaltrials.gov/ct2/show/NCT04869774

**International Registered Report Identifier (IRRID):**

DERR1-10.2196/26717

## Introduction

### Background and Rationale

Surgical site infections (SSIs) are the most common nosocomial infection among surgical patients, occurring in 5.5% of surgical cases at our institution, The Ottawa Hospital [1]. Similar rates are seen at other centers across North America and Europe, with SSIs impacting 3%-5% of inpatient surgical cases and accounting for 20%-38% of nosocomial infections among surgical patients [2-5]. Patients undergoing colorectal surgery are disproportionately affected. A recent study at our institution found that 24% of patients undergoing colorectal surgery developed an SSI [6]. SSIs are associated with significant morbidity and mortality both in the short and long term. In the initial postoperative period, SSIs are associated with increased postoperative mortality, length of stay, and intensive care unit admission. In the long term, SSIs are independently associated with higher readmission and mortality rates compared to those without an SSI [1].

### SSIs and a Need for Postoperative Surveillance

Approximately two-thirds of SSIs are defined as superficial, meaning they involve only the skin and subcutaneous tissues [5]. These SSIs are detectable by clinical exam; when identified early, they can be managed with wound management alone. However, approximately 57% of SSIs are diagnosed after discharge from hospital, when patients are no longer regularly examined by a clinician [7]. When comparing patients with SSIs detected after discharge from hospital to those with SSIs detected in hospital, the former are more likely to have an advanced infection at time of detection and experience poorer quality of life, greater physical limitations, and lower mental health component scores, as well as have increased outpatient and emergency department (ED) visits, hospital readmissions, and higher demand for diagnostic imaging [8,9]. The incidence and morbidity of an SSI can be reduced by regular clinical surveillance of the incision [10].

### Mobile App Technology

Mobile apps are an effective and desirable method for assisting patients with self-monitoring for SSIs and other complications after surgery [11]**.** Photo-based mobile apps have been shown in multiple studies to be effective at detecting superficial SSIs [12-14]. This can also reduce a patient’s need for in-person visits by facilitating virtual monitoring and virtual visits with a clinician. This is critical in the context of the COVID-19 pandemic, and could reduce ED visits and readmission in the postoperative period [15]. Finally, the postoperative period can be stressful and isolating for patients. Patients using mobile apps for surveillance after surgery have reported a greater sense of empowerment, as well as more engagement and satisfaction [16].

The Health Outcomes Worldwide how2trak (H2T) app is an example of a mobile point-of-care technology for wound surveillance. H2T has been shown to be an effective tool for postoperative monitoring after discharge from hospital following a cesarean delivery. However, this app has not been assessed among colorectal surgery patients, who represent a more diverse, comorbid, and older population than young females undergoing cesarean delivery [17]. H2T has been adopted at The Ottawa Hospital for wound monitoring in the vascular surgery patient population, and plans are underway to integrate it with the hospital electronic medical record system. H2T could potentially enhance postoperative monitoring and detection of superficial SSI but would require a significant change in workflow to the multidisciplinary care of wound complications. Therefore, its feasibility must be assessed prior to conducting a trial to assess its effectiveness in this population.

### Objectives

This study aims to assess the feasibility of a randomized controlled trial where patients discharged from hospital after colorectal surgery are randomized to have virtual monitoring of their surgical incision(s), symptoms, and ostomy using the H2T app or to standard of care. The primary outcome is feasibility as measured by enrollment, randomization, H2T usability, data extraction, and resource capacity.

This is intended to inform the development of a definitive trial to establish if the H2T app enhances SSI detection, improves patients’ experience, and reduces the risk of COVID-19 transmission compared to standard care.

## Methods

### Overview

This protocol was developed in accordance with the SPIRIT (Standardized Protocol Items: Recommendations for Interventional Trials) statement [18] and CONSORT-EHEALTH (Consolidated Standards of Reporting Trials of Electronic and Mobile Health Applications and Onine Telehealth) reporting recommendations [19]. This study has been approved by the Research Ethics Board at the Ottawa Hospital Research Institute (20200596-01H).

### Study Setting

This study will be conducted with the Ottawa Colorectal Group within the Division of General Surgery at The Ottawa Hospital, a multisite academic hospital in Ottawa, Ontario, Canada.

### Trial Design

This is an unblinded feasibility randomized controlled trial. Eligible patients will be randomized 1:1 to receive virtual monitoring of their surgical incision, symptoms, and ostomy using H2T or to standard of care.

### Eligibility Criteria

All patients being discharged from hospital after undergoing urgent, semiurgent, or elective abdominal surgery by a colorectal surgeon at The Ottawa Hospital will be considered for participation in the study.

To be included in the study, participants must be ≥16 years of age, patients who are being discharged from hospital after undergoing semiurgent, urgent, or elective abdominal surgery by a colorectal surgeon at The Ottawa Hospital, and have provided informed consent to participate. Patients enrolled in other clinical trials will still be candidates for this feasibility trial.

Patients will be excluded if they are <16 years of age, have no access to or ability to use a mobile device, have no cellular data/Wi-Fi access, and/or cannot read and write in English.

Clinicians using the H2T app in this study will be considered study participants as well. They will be asked to complete the Modified Post-Study System Usability Questionnaire (PSSUQ) for Patients and Clinicians, a survey derived from the PSSUQ by Lewis and colleagues [20]. This survey addresses the experience of using the H2T app; their feedback regarding usability is fundamental for future improvement.

### Informed Consent

The colorectal surgery team will notify the research assistant of all patients undergoing urgent, semiurgent, or elective abdominal surgery by a colorectal surgeon at The Ottawa Hospital who are potentially eligible for participation within 72 hours following the patient’s surgery. The research assistant will then meet with patients by phone or in person to screen for eligibility, and proceed with the consent discussion, which will include the following: the nature of the trial, eligibility criteria, and the risks and benefits of participating. The research assistant will also assess their willingness to participate, and explain that their data may be included in a full-scale randomized controlled trial if completed as a vanguard study.

Clinicians who have used H2T during the study period will be contacted by email by the research assistant and will be invited to complete the Patient and Clinician Survey of Application survey. The completion of the survey will indicate their acceptance to participate in the study.

### Interventions

Immediately after consent is obtained, eligible patients will be randomized 1:1 to two arms (Figure 1).

**Figure 1 figure1:**
[figure not shown]
CONSORT flow diagram.

Intervention group patients will undergo virtual monitoring of their incision and symptoms using H2T. Early in their postoperative course, patients will be guided through developing a login and instructed on how to download and use H2T by the research assistant. In developing their login, patients will enter their full name and partial date of birth (MM-YYYY), which will be used as identifiers to link to The Ottawa Hospital data. Using the H2T app, patients will be asked to answer a series of questions (see Patient Application Questionnaire in Multimedia Appendix 1) and photograph their surgical incision on postoperative day 3, 5, 7, 10, 20, and 30 through the app (see timeline in Table 1). Patient responses and photographs entered into the H2T app on the patient’s mobile device will be reviewed within 72 hours by a trained Nurse Specialized in Wound, Ostomy, and Continence (NSWOC) [21] who will be trained to triage patients using the algorithm in Figure 2. If a concern is identified, the NSWOC will contact the patient to arrange a virtual visit using the H2T app or notify the surgery team (including colorectal surgeons and physician residents) in accordance with the algorithm, clinical discretion, and scope of practice. Patients will be reminded that it may take up to 72 hours to receive a response from the NSWOC; accordingly, if they have urgent concerns or emergency, they should present to the ED or call 911.

Control group patients will receive no virtual monitoring. No virtual monitoring is currently in place as part of standard of care after colorectal surgery at The Ottawa Hospital. Therefore, standard of care without any virtual monitoring was selected as the comparator.

Both groups will receive routine standard of care. Standard of care will involve a routine postoperative follow-up with the surgical team 4-6 weeks after discharge from hospital.

Patients and clinicians will complete the PSSUQ, a validated 16-item survey to assess the perceived learnability, efficiency, and errors of H2T, as well as user satisfaction with the app [20,22] (see Multimedia Appendix 1). Patients will also submit a survey to assess their satisfaction with their postoperative care at postoperative day 30 to assess their perceived experience of their postdischarge care using a modified version of PATSAT32, a validated questionnaire for patients undergoing gastrointestinal surgery [23,24] (see Multimedia Appendix 1). The intervention will be reviewed every two months by the investigator team and General Surgery Comprehensive Unit-based Safety Program team. H2T functionality will remain consistent throughout the study, with revisions made only in response to unexpected events.

**Table 1 table1:** Participant timeline.

Timepoint		Study period									
		Visit with research assistant	Visit with research assistant	Intervention period (postoperative day 3-30)							Close-out
		–*t*_1_	0-3	3	5	7	10	20	30	*t* _x_	
**Enrolment**											
	Eligibility screen	✓	✓								
	Informed consent	✓	✓								
	Allocation		✓								
**Interventions**											
	How2Trak virtual monitoring			✓	✓	✓	✓	✓	✓	✓	
	Control								✓	✓	
**Assessments**											
	Baseline comorbidities	✓	✓								
	Health system interaction			✓	✓	✓	✓	✓	✓	✓	
	Postoperative outcomes			✓	✓	✓	✓	✓	✓	✓	
	Patient experience								✓	✓	
	App usability									✓	

**Figure 2 figure2:**
[figure not shown]
Nurse Specialized in Wound, Ostomy, and Continence (NSWOC) triage. Wound And Symptom Tracking After Colorectal Surgery Using How2trak (WATCH) study NSWOC workflow process. Urgent refers to a concern that requires immediate medical attention. ED: emergency department; H2T: how2trak; SSI: surgical site infection (based on the Centers for Disease Control and Prevention definition, see Patient Application Response suggestive of surgical site infection).

### Strategies to Improve Adherence to the Intervention

Patients will receive notifications through the app to serve as a reminder each day that a photo and questionnaire are required. If no response is received, the research assistant will follow up with the patient by email and/or by phone. In keeping with the pragmatic nature of this trial, patients may request to withdraw from the intervention group at any time.

### Outcomes

#### Primary Outcome: Feasibility

This study will assess the feasibility of a definitive trial by assessing specific outcome measures that will be determined to be feasible if all endpoints are met:

Capability for enrollment will be assessed to determine recruitment potential and an optimal sample size estimation for a full-scale randomized controlled trial, by measuring the following outcomes: proportion of patients screened, proportion of eligible patients consenting to involvement in this study, and proportion of recruited patients who are enrolled in the study.Endpoint: 4 patients per month on average are enrolled in the study.Feasibility of the randomization processes will be evaluated, including the proportion of patients randomized who receive the intervention.Endpoint: 90% of patients enrolled are randomized to the intervention or control group.How2trak usability, delivery, and compliance will be evaluated by assessing patients’ and health care providers’ perceived usability of the technology, as well as the number of questionnaires and photos completed by each patient during the postoperative period.Endpoints: Patients completed, on average, 60% of self-assessments. The mean score of the H2T app in patient and clinician surveys is >2.Feasibility of data extraction, measured by the proportion of participants for which all relevant outcomes of a full-scale randomized controlled trial were documented.Endpoint: All primary outcomes of the definitive trial (see “Definitive Trial Outcomes” section below) are recorded for 80% of patients.Resources and time required to conduct the feasibility trial will be assessed. In particular, the administrative capacity, expertise, skills, space, and time of the research team, the feasibility of the designated budget, and the compliance of interdisciplinary staff with the study protocol will be assessed.Endpoint: The feasibility study is completed with the allocated interdisciplinary staff.

#### Definitive Trial Outcomes

The primary outcomes for a definitive trial collected in this study will compare the SSI incidence and severity of patients in the two study arms, as well as their experiences. An SSI is an infection that occurs after surgery in the part of the body where the surgery was performed. A superficial incisional SSI is an infection that involves only skin or subcutaneous tissue of the surgical incision and will be defined using the Centers for Disease Control and Prevention criteria [5].

Secondary outcomes for a definitive trial include hours of in-person interactions with the health care system (including readmissions to hospital, ED visits, and clinic visits), confirmed COVID-19 infection within 30 days after surgery, incidence of postoperative adverse events, and incidence and characterization of ostomy complications.

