### Data Collection and Management

Data will be captured through the assessments and/or photographs in H2T and the hospital’s electronic health information system (Epic). Data sent from H2T to The Ottawa Hospital—including patient identifiers to allow for merging with Epic data—will be transferred through a secure, access-controlled folder within Office 365. Once the data files are merged, they will be deidentified. Only research personnel will have access to the study data. A data monitoring committee will not be developed given the minimal risk and small sample size of this feasibility trial.

If a definitive trial is completed, we plan to incorporate the results of this study into the data collection of the trial.

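### SSI is looked for more intensively in the H2T arm than in controls, so comparing SSI incidence and severity can show a difference without a true effect, and the pooled 80% data endpoint cannot reveal it

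*Protocol article*

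**What the plan says.** **Outcome.** Under Definitive Trial Outcomes, the primary outcomes collected here "will compare the SSI incidence and severity of patients in the two study arms", together with patient experience. CDC criteria are named for superficial incisional SSI, without distinction by arm.

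**Surveillance.** Under Interventions, H2T patients answer questions and photograph the incision on days 3, 5, 7, 10, 20 and 30. A wound nurse reviews each entry within 72 hours, and a concern leads to a virtual visit or a notice to the surgical team. Under Strategies to Improve Adherence, the research assistant chases missed entries by email or phone. By contrast, "Control group patients will receive no virtual monitoring". Both arms share a "routine postoperative follow-up with the surgical team 4-6 weeks after discharge from hospital".

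**Data sources.** "Data will be captured through the assessments and/or photographs in H2T" and the hospital record (Epic). The Confidentiality section says hospital data come primarily from Epic. The trial is unblinded.

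**Aim.** The abstract's objective is to see whether the app can "increase detection of SSIs after colorectal surgery", and the Objectives section likewise names enhanced SSI detection. The background states: "The incidence and morbidity of an SSI can be reduced by regular clinical surveillance of the incision".

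**Data endpoint.** Under Primary Outcome: Feasibility, data extraction succeeds if all primary outcomes of the definitive trial "are recorded for 80% of patients". No threshold is set by arm.

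**Later use.** If a definitive trial is completed, the investigators plan to incorporate these results into it (Data Collection and Management). Informed Consent says the data may be included.

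**The concern.** The intervention is also a means of finding the outcome. The protocol puts about 57% of SSIs after discharge, when regular examination by a clinician has stopped, and describes about two-thirds of SSIs as superficial. Such cases are what an app with photographs can add, and what routine care may leave undocumented.

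A higher SSI rate with H2T could then mean better detection (success) or more infection (harm). A lower rate could mean prevention. A null result could be better detection and fewer infections cancelling out. A single outcome called incidence cannot distinguish these. Severity among detected SSIs has a related problem: if H2T adds mainly mild cases, its SSIs look milder on average although no patient is better off.

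What is at stake is the main comparison of the definitive trial, plus any data from this study carried into it. The data-extraction criterion is the one feasibility check on whether these outcomes can be captured, and it can pass while capture in controls is poor. SSI status not collected from controls now may not be recoverable later.

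**Working it through.** The protocol gives no sample size, power or event count for SSI, so there is no figure of its own to reproduce. What follows is an illustration.

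**Inputs from the Protocol article**
- SSI incidence p after colorectal surgery: 16.3% (Abstract, Background) or 24% (Introduction, Background and Rationale).
- Share of SSIs diagnosed after discharge: 57%. Superficial share: about 2/3 (both from SSIs and a Need for Postoperative Surveillance).
- Allocation 1:1 (Trial Design).

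**Assumptions not in the documents**
- True incidence is equal in both arms.
- SSIs diagnosed before discharge (43%) are captured fully in both arms.
- The share of post-discharge SSIs captured is h with H2T and c in controls.

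**1. Incidence.** Observed rate = p × (0.43 + 0.57 × capture), so the spurious difference (H2T minus control) = 0.57 × p × (h − c).

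| p | h | c | Difference in points |
|---|---|---|---|
| 16.3% | 100% | 90% | 0.57 × 16.3 × 0.10 = +0.9 |
| 16.3% | 100% | 60% | 0.57 × 16.3 × 0.40 = +3.7 |
| 24% | 100% | 90% | 0.57 × 24 × 0.10 = +1.4 |
| 24% | 100% | 60% | 0.57 × 24 × 0.40 = +5.5 |
| 16.3% | 80% | 60% | 0.57 × 16.3 × 0.20 = +1.9 |
| 16.3% | 80% | 90% | 0.57 × 16.3 × (−0.10) = −0.9 |
| 24% | 80% | 60% | 0.57 × 24 × 0.20 = +2.7 |
| 24% | 80% | 90% | 0.57 × 24 × (−0.10) = −1.4 |

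Equal capture gives a difference of 0. The rows with h = 80% matter because the feasibility criteria accept an average of 60% of self-assessments completed, so full capture with H2T is not assured.

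**2. Severity among detected SSIs.** Suppose controls miss only superficial post-discharge SSIs, and the superficial share is 2/3 both before and after discharge. With c now the capture of those cases:

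Control superficial share = (2/3)(0.43 + 0.57c) / [(2/3)(0.43 + 0.57c) + 1/3]

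- c = 80%: 0.5907 / 0.9240 = 63.9%
- c = 60%: 0.5147 / 0.8480 = 60.7%

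With full capture on H2T the share is 66.7%. Control SSIs look more severe with no true change.

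**3. The 80% endpoint.** With 1:1 allocation, (100 + 60)/2 = 80% and (95 + 65)/2 = 80%, so both splits pass. Completeness is also not sensitivity: if an undetected SSI were entered as no SSI, both arms could be 100% complete and still unequal in capture.

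**4. Timing of the shared visit.** The earliest visit is 28 days after discharge. For discharge on postoperative day 3 or later it falls on day 3 + 28 = 31 or later, after the last app check.

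**Rejection rates.** These depend on a sample size that the protocol does not give. If all 80 anticipated eligible patients enrolled (about 40 per arm), then with full H2T capture and 70% control capture a two-sided 5% test would reject in about 6-7% of trials, close to nominal. Rates for a larger trial would rest on an invented sample size and are left out.

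**The case against.** **Detection is the intended effect.** The abstract and the Objectives section both say so, so extra SSIs found through the app are largely what the trial is looking for. This stands, and it is why the problem is not simply bias. But the outcome is worded as incidence and severity, so the planned comparison does not isolate the effect that the aim names. The sentence about surveillance reducing incidence is background, not a trial hypothesis; it shows only that an effect in the other direction is plausible.

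**Control follow-up is not empty.** Hospital data come primarily, not solely, from Epic. Table 1 lists postoperative outcomes for days 3-30 without limiting them to one arm. The shared visit, though after day 30, can take a history of the whole window. A reader might infer that any control SSI treated elsewhere or healed by then counts as no SSI, or that a blank record counts as recorded. The documents say neither, nor do they say that an app entry alone counts as an SSI.

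**The direction is not fixed.** A reader might infer that the app must create an excess. That needs better capture with H2T than in controls, and the sign can reverse when H2T capture is incomplete.

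**This is a feasibility study and a condensed article.** Analysis here is descriptive, carry-forward is conditional, and adjudication details may sit in the full protocol. This lowers the urgency. It does not supply equal ascertainment: adjudicating records cannot recover SSIs that were never recorded, and the endpoint as printed has no threshold by arm.

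**Conclusion.** The point holds as a risk that the stated design leaves open. Surveillance differs by arm, the outcome wording merges detection with incidence, and the pooled 80% criterion cannot show unequal capture.

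Under the assumptions of equal true incidence, full H2T capture and 60-90% control capture of post-discharge SSIs, the spurious excess is 0.9-3.7 points at 16.3% incidence or 1.4-5.5 points at 24%. With 80% H2T capture it ranges from +1.9 to −0.9 points or from +2.7 to −1.4 points. The capture rates are assumptions, so these figures show possible scale and are not an estimate.

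This should be fixed, but it does not invalidate the present study, whose own primary outcome is feasibility. It becomes serious if these data enter a definitive trial with the outcome defined as it is now.

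**What to change.** 1. **Common ascertainment.** Add the same CDC-based SSI items to the day-30 patient survey in both arms. Classify SSI in both arms by one rule, from sources common to both (the hospital record plus these items). Report app-triggered detections separately as the detection outcome. State that this reduces but does not remove detection bias: app-triggered visits and notices can also produce diagnoses in Epic, and a patient told of an SSI can report it at day 30.
2. **Outcome wording.** Under Definitive Trial Outcomes, name SSI detection and SSI incidence as separate outcomes. Compare severity across all randomised patients (none / superficial / deep / organ-space), not only among detected SSIs.
3. **Endpoint.** Replace the data-extraction criterion, as it applies to SSI, with: SSI status positively documented (yes or no) to day 30 in at least 80% of patients in each arm.

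**Cost.** A protocol amendment and a few items on a survey already planned for day 30, with no added visit. The endpoint becomes harder to pass.
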